### Adverse events

The investigators will report all Adverse Events (AE) immediately to the sponsor or his legal representative except for those that the protocol or investigator's brochure identifies as not requiring immediate reporting.

An "adverse event" is any untoward medical occurrence in a patient or clinical trial subject administered a medicinal product and which does not necessarily have a causal relationship with this treatment.

Serious adverse events (SAE) are any untoward medical occurrence of effect that at any dose results in death, is life-threatening, requires hospitalization or prolongation of existing inpatients' hospitalization, results in persisting or significant disability or incapability, or is a congenital abnormality or birth defect.

For all serious adverse events, the documents and patient data must be verified by the responsible study personnel.

Patients' toxicities are to be classified and documented according to the NCI Common Toxicity Criteria (CTC). Toxicity is documented weekly during RCHT and prior to every application of Cetuximab as well as at every follow-up visit.

### Medication

All TMZ applications are provided by the pharmacy of the University of Heidelberg. Cetuximab is provided by Merck KGaA, Darmstadt, and is stored until clinical application by the pharmacy of the University of Heidelberg. All study medication is prepared especially for each patient registered into the study and is delivered to the Department of Radiation Oncology at short notice before administration.

### Monitoring

Monitoring is performed by the Klinische Koordinierunszentrum für Studien (KKS) of the University Hospital in Heidelberg according the guidelines of Good Clinical Practice (GCP) and the German law on drug safety (Arzneimittelgesetz, AMG).

### Ethics, informed consent and safety

For the present study the Eudract-Number 2005-003911-63 has been obtained. The final study protocol has been approved by the ethics committee of the University of Heidelberg, Heidelberg, Germany (Protocol Number AFmo-323/2005 [31]) as well as by the Paul Ehrlich Institute (PEI; registration number 119/01). This protocol follows all requirements of the Declaration of Helsinki in the recent German version (Somerset West Version, 1996).

The study protocol is in accordance with the principles of Good Clinical Practice (GCP) guidelines and the Federal Data Protection Act. The trial has been initiated and will be carried out following all local legal and regulatory requirements. The medical secrecy act is also followed.

Of each patient recruited into the study, written informed consent is essential prior to inclusion into the study after extensive information about the intent of the study, the study regimen, potential associated risks and side effects as well as potential alternative therapies. Until the patient has given written informed consent, no action aiming at inclusion into the study protocol, especially any diagnostic measures required, will be taken.

### Quality of life-assessment

Assessment of quality of life is one of the secondary objectives of the trial. The EORTC QLQ30 is a general measure of quality of life in cancer patients. The questionnaire consists of 9 multi-item scales: five functional scales (physical, role, cognitive, emotional and social), three symptom scales (fatigue, pain and nausea/vomiting) as well as global health and quality of life scale [32]. Specific symptoms including dyspnoea, insomnia, anorexia, constipation, diarrhoea and financial impact are measure as six single items. This questionnaire has been used widely in studies with cancer patients and is able to distinguish between individuals with metastatic and non-metastatic disease, as well as between patients at different stages of their illness. Previous studies have proven this tool to have good internal consistency (alpha > 0.70) and good test-re-test-reliability (0.80 to 0.90) [33].

This test will be performed at the initiation of RCHT, during the course of the treatment and at every follow-up visit.

### Follow-up

Patients are seen for follow-up 6 weeks after completion of RCHT with cetuximab, thereafter in three-months intervals or as needed clinically. During adjuvant treatment, blood values will be evaluated weekly.

All follow-up visits include complete neurological assessment as well as contrast-enhanced MRI- and/or CT-scans. Quality of life assessment will be performed at each follow-up visit.

Additional examinations including FDG- or FLT-PET will be scheduled as required.

### Treatment at tumor progression

In order to distinguish between radiation-induced side effects and tumor progression, FDG-PET and FLT-PET examinations will be scheduled as required.

In case of tumor recurrence during combined RCHT with cetuximab or during adjuvant treatment with TMZ, this therapy will be stopped.

In every case of recurrence, the possibility of neurosurgical intervention will be evaluated. Additionally, it will be evaluated whether re-irradiation can be applied safely; moreover, treatment with standard chemotherapeutic substances will be evaluated in every patient.

### Interim analysis

An interim analysis is planned after inclusion of 15 patients into the main study. The trial can be stopped should it be obvious that the alternative hypothesis of a tolerable toxicity rate

H1:R≤10% i.e. NONTOX-Rate ≥90%

cannot be achieved, i.e. should the number of WHO grade III and IV toxicities be larger than 7 (meaning 8 or more Grade III and IV toxicities). In this case the study will be closed due to "futility".

Recruitment for the study will be conducted during a period of 2 years. Final evaluation of the primary and secondary endpoints of the study will be performed 1 year after inclusion of the last patient.

The formal end of the study is defined as the end of the observation period of the last patient included into the study.

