### Study objectives

Primary endpoint of the study is feasibility and toxicity of combined trimodal therapy with TMZ, cetuximab and radiotherapy. According to the current standard treatment for patients with GBM, about 10% off all patients develop WHO Grade III and IV toxicity [9]. We defined a toxicity rate of 30% for WHO Grade III and IV side effects as overall acceptable for this study.

Secondary endpoints include overall survival, progression-free survival and quality of life.

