### Statistical calculations for trial sample size

The trial is evaluating in its Phase 1 part the tolerability of the TMZ dose of 75 mg/m^2 ^together with cetuximab in a two step escalation with a maximum of 12 patients, while evaluation in its Phase II part the following two hypotheses:

1. non-tolerable toxicity H0: existence of no tolerable toxicity, i.e. TR >30%, NTR ≤70%

2. tolerable toxicity H1: existence of tolerable toxicity, i.e. TR < 10%, NTR ≥90%

with RT denoting the rate of toxicity and NTR the rate of non-toxicity. Therefore, the trial consists of a dose finding part (Phase I) and a feasibility part (Phase II).

These two hypothesis will be examined using a two-step optimal phase II design according to Simon et al. [30] in the defined patient population with a significance level of 5% (alpha = 0.05) and a power of 90% (beta = 0.1) with a one-armed analysis in this single arm trial.

To demonstrate tolerability of the toxicity with a hypothesis-test between NONTOX of 70% versus the anticipated NONTOX of 90% within a One-Step-Phase II Design, 36 evaluable patients are required (NCSS PASS 2000).

We calculated a drop-out rate of 10%, and therefore a projected patient number of 40 is planned.

With inclusion of the 6 patients for the dose-finding part of the protocol, a maximum of 46 patients will be included into the study.

Recruitment will be carried out over 2 years and a follow-up time of 1 year per patient is required to evaluate the primary endpoint.

Overall survival will be determined as the time span between primary diagnosis and death of lost to follow-up (censored observation). Progression-free survival will be determined as the time span between start of the treatment and tumor progression or death, whatever occurred first or an event which characterises a censored observation.

The trial consists of a dose-finding study (part 1; Phase I) followed by a Phase II component.

#### Step 1

3 patients are treated with combined RCHT (RT at dose level 1 (DL1) with a total dose of 60 Gy in 2 Gy single fractions + TMZ 50 mg/m^2^/day, 6 weeks)

Cetuximab (ERBITUX^®^) is applied in a dose of 400 mg/m^2 ^in week 1, thereafter weekly at 250 mg/m^2 ^week during the course of RCHT.

Adjuvant treatment: 6 cycles of TMZ 150 mg/m^2^/day for 5 days, every 28 days (q28d)

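### The interim stopping limit counts grade III/IV toxicities although the hypotheses are per patient, and endpoint and records name different grading systems

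*Protocol article*

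**What the plan says.** **Unit.** The Interim analysis section of the protocol article fixes the timing: "An interim analysis is planned after inclusion of 15 patients into the main study". The trial may then be closed for futility "should the number of WHO grade III and IV toxicities be larger than 7 (meaning 8 or more Grade III and IV toxicities". Both halves of that statement, the second being the gloss "meaning 8 or more Grade III and IV toxicities", count toxicities; neither says patients with a toxicity.

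The rates that this limit serves are per patient. Study objectives gives the benchmark under standard treatment: "about 10% off all patients develop WHO Grade III and IV toxicity". The section on sample size states the null hypothesis as "H0: existence of no tolerable toxicity, i.e. TR >30%, NTR ≤70" percent, sets a toxicity rate below 10% against it, and sizes the trial at 36 evaluable patients.

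**Scale.** Study objectives sets the acceptable level on WHO grades: "We defined a toxicity rate of 30% for WHO Grade III and IV side effects as overall acceptable for this study". The interim rule also names WHO grades. The Adverse events section names a different system: "Patients' toxicities are to be classified and documented according to the NCI Common Toxicity Criteria (CTC". No section maps one scale to the other or says that WHO grades are recorded as well.

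**The concern.** A toxicity rate and a non-toxicity rate that add to 100% describe patients, each of whom either has or has not had a grade III/IV toxicity. Events do not behave like that, because one patient can contribute several. The Adverse events section has toxicity documented weekly during radiochemotherapy, before each cetuximab application and at every follow-up visit, so several entries per patient are to be expected. A limit on events therefore has no fixed link to a hypothesis about patients, and the chance of closing the trial wrongly cannot be stated. The section says that the study will be closed once the limit is met, so two people applying the same text to the same data could reach opposite decisions.

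The scale conflict is a separate matter and reaches the primary endpoint itself. If the endpoint is defined on one grading system and the records name another, whoever does the analysis has to choose between them, and the document does not say how.

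**Working it through.** **1. What unit does the design use?**

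Inputs from the section on sample size: non-toxicity 70% versus 90%, alpha 0.05 (taken as one-sided, since the side is not stated), power 0.90, Simon optimal two-stage design.

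An exact search with the patient as the unit gives 15 patients in stage 1 and 36 in total. The design stops at 11 or fewer non-toxic patients of 15 and succeeds at 30 or more of 36:

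- alpha = Σ over x = 12 to 15 of P(X₁ = x) · P(X₂ ≥ 30 − x), with X₁ ~ Bin(15, 0.70) and X₂ ~ Bin(21, 0.70), = 0.046
- power = the same sum at 0.90 = 0.905

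This reproduces both the stated 36 evaluable patients and the interim at 15. Allowing for 10% drop-out, 36 / 0.90 = 40, also as stated. The design is binomial in patients.

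**2. The interim rule if patients are counted**

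P(stop) = P(X ≥ 8) with X ~ Bin(15, p):

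| True patient rate p | P(stop) |
|---|---|
| 10% | 0.00003 (0.003%) |
| 20% | 0.0042 |
| 30% | 0.0500 |

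**3. The interim rule if events are counted, as worded**

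This needs the number of grade III/IV events per toxic patient, which the document does not give. Assume each toxic patient has 1 + Poisson(m − 1) events, a mean of m. Given X toxic patients, the total is X + Poisson((m − 1)X), and P(stop) is the probability that this total is 8 or more:

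| p | m = 2 | m = 3 |
|---|---|---|
| 10% | 6.4% | 20.4% |
| 20% | 30.7% | 57.3% |
| 30% | 61.3% | 83.5% |

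A simpler assumption, the same number of events in every toxic patient, points the same way. At p = 10%:

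- 2 events each: 8/2 = 4 toxic patients trigger the rule; P(X ≥ 4) = 5.6%
- 3 events each: 8/3 rounds up to 3 patients; P(X ≥ 3) = 18.4%
- 4 events each: 8/4 = 2 patients; P(X ≥ 2) = 45.1%

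A single case shows the problem without any distribution. Eight events in 3 of 15 patients is a patient rate of 3/15 = 20%, below the 30% boundary of the null hypothesis, yet it meets the literal limit.

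**4. The scale**

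There is no figure to recompute. Study objectives and the interim rule say WHO; Adverse events says NCI CTC. The document describes neither system's grade boundaries, so the effect of the mismatch on the toxicity rate cannot be derived from it.

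**The case against.** The best reply on the unit is that toxicities is loose wording for patients with a toxicity. The limit directly follows a restatement of the alternative hypothesis as a non-toxicity rate of at least 90%, and is offered as its working form. The arithmetic supports this: 8 or more of 15 patients has probability 0.050 at a 30% rate, which equals the stated alpha, as one would expect of a binomial limit on patients. I accept that a patient count was probably intended. But the document does not derive the limit, no sentence says that patients are counted, and the parenthesis meant to clarify the limit repeats the event wording.

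A reader might go further and infer that the primary test itself is in the wrong unit. The document does not support that: the final hypotheses are rates and the sample size is in evaluable patients. Nor should the event-based probabilities be read as the trial's operating characteristics. The events per toxic patient and the Poisson form are assumptions, and the results move with them.

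On the scale, a reader might infer that WHO grades are not recorded at all. The article does not say so. Adverse events is a general section of a condensed article, and WHO grades could also be assigned for the endpoint. What stands is that the text names two systems for the same toxicities and does not connect them.

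It is also fair to say that moving to NCI CTC is not free, because the benchmark is WHO-graded. That is a reason to ask for reconciliation and not to dictate the choice.

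**Conclusion.** Both parts hold, within limits. The interim limit is worded as a number of events while the hypotheses and the design are per patient, so as written it has no defined error rate. At a true patient rate of 10%, the chance of stopping is 0.003% if patients are counted and about 6% to 20% if events are counted, the latter resting on an assumed mean of 2 to 3 events per toxic patient. The fault is confined to the interim rule; the final test and the sample size of 36 stand.

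The WHO versus NCI CTC conflict is a contradiction in the text about how the primary toxicity endpoint is graded. Its numerical effect is unknown from the document.

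This should be corrected because it concerns a rule that can close the trial and the definition of the primary endpoint, but it does not undermine the design.

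**What to change.** In Interim analysis, state the count as the number of patients, among the 15, with at least one grade III or IV toxicity. Define the primary variable in the same words in Study objectives.

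Reconcile Study objectives, Adverse events and Interim analysis to one named grading system. If NCI CTC is kept, add that the 10% benchmark is WHO-graded and so not strictly comparable. If WHO is kept for the endpoint, say that WHO grades are recorded, or how they are obtained from the NCI CTC records.

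The change of unit costs wording only, since toxicity is already documented for each patient. Keeping NCI CTC has a small downside: the endpoint moves off the scale of its benchmark.

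One related check while editing: correcting the unit does not reconcile the limit itself with the design. The Simon design that reproduces 15 and 36 stops at 11 or fewer non-toxic patients of 15, which is 15 − 11 = 4 or more toxic patients, whereas the interim limit is 8. The section on sample size and the interim section should be reconciled on this too.

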**Methods/design:**

GERT is a one-armed single-center phase I/II trial. In a first step, dose-escalation of TMZ from 50 mg/m^2 ^to 75 mg/m^2 ^together with radiotherapy and cetuximab will be performed. Should safety be proven, the phase II trial will be initiated with the standard dose of 75 mg/m^2 ^of TMZ. Cetuximab will be applied in the standard application dose of 400 mg/m^2 ^in week 1, thereafter at a dose of 250 mg/m^2 ^weekly. A total of 46 patients will be included into this phase I/II trial.

Primary endpoints are feasibility and toxicity, secondary endpoints are overall and progression-free survival. An interim analysis will be performed after inclusion of 15 patients into the main study. Patients' enrolment will be performed over a period of 2 years. The observation time will end 2 years after inclusion of the last patient.

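### The final OS and PFS evaluation is dated 1 year after the last inclusion, although observation is planned to run for 2 years, so the second year enters no stated final survival analysis

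*Protocol article*

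**What the plan says.** Four places in the protocol article bear on the timing.

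- **Interim analysis:** "Final evaluation of the primary and secondary endpoints of the study will be performed 1 year after inclusion of the last patient". The same section closes with "The formal end of the study is defined as the end of the observation period of the last patient included into the study", without giving the length of that period.
- **Abstract, Methods/design:** "The observation time will end 2 years after inclusion of the last patient". Accrual is given there too: "enrolment will be performed over a period of 2 years".
- **Statistical calculations for trial sample size:** "Recruitment will be carried out over 2 years and a follow-up time of 1 year per patient is required to evaluate the primary endpoint".
- **Study objectives:** "Secondary endpoints include overall survival, progression-free survival and quality of life".

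The 1-year date therefore covers OS and PFS as well as toxicity. The article mentions no later or updated survival analysis and does not relate the 1-year date to the 2-year date.

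**The concern.** The article gives a reason for 1 year only for the primary endpoint. It gives none for survival, yet the same date closes the evaluation of OS and PFS. Read as written, patients stay under observation for a further year after the only final survival analysis that is described.

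The abstract's Discussion gives the trial's goal as safety and efficacy, and OS and PFS carry the efficacy part. In a single-arm trial of about 40 patients, a few deaths more or fewer change how well the later part of the survival curve is known. The patients enrolled last have only about 12 months of follow-up at the early cut. That is shorter than the median OS in both temozolomide studies that the Background cites, 14.6 and 19 months.

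**Working it through.** **Inputs from the article**
- Accrual A = 24 months (abstract; sample-size section).
- Minimum follow-up F = 12 months (Interim analysis) or 24 months (abstract).
- Median OS in earlier studies: 14.6 months (randomized trial, chemoradiotherapy arm) and 19 months (the centre's own series), both in the Background. The trial states no expected OS of its own.
- N = 40 planned in phase II.

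**Assumptions:** uniform accrual, exponential survival, no dropout, follow-up counted from inclusion.

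**The plan's own figures.** The article states no survival figure, so there is none to reproduce. Its sample size does reproduce. For non-toxicity of 70% against 90%, alpha 0.05 and power 0.90, a search for Simon's optimal two-stage design gives 36 patients with 15 in the first stage (alpha 0.046, power 0.905). Then 36/(1 − 0.10) = 40, and 40 + 6 = 46. The point below concerns a date and leaves these numbers unchanged.

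**Step 1. Deaths observed at each cut.** With λ = ln 2 / median, the expected share of deaths observed is

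1 − [exp(−λF) − exp(−λ(A+F))] / (λA).

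- Median 14.6 (λ = 0.04748), F = 12: 1 − (0.5657 − 0.1810)/(0.04748 × 24) = 0.662. F = 24: 1 − (0.3200 − 0.1024)/(0.04748 × 24) = 0.809.
- Median 19 (λ = 0.03648), F = 12: 1 − (0.6455 − 0.2689)/(0.03648 × 24) = 0.570. F = 24: 1 − (0.4166 − 0.1736)/(0.03648 × 24) = 0.722.

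| Median OS | Deaths of 40, 1-year cut | Deaths of 40, 2-year cut | Difference |
|---|---|---|---|
| 14.6 months | 26.5 | 32.4 | 5.9 |
| 19 months | 22.8 | 28.9 | 6.1 |

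If all 46 patients are counted, the differences are 6.7 and 7.0.

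**Step 2. Precision along the curve.** The large-sample Greenwood form is SE(t) = S(t)·√(V(t)/N), with V(t) = ∫₀ᵗ λ/[S(u)G(u)] du. G(u) is the share of patients with potential follow-up of at least u: 1 up to F, then (A + F − u)/A. With F = 24 there is no administrative censoring before 24 months, so V(t) = 1/S(t) − 1.

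| Time point | Median OS | V, 1-year cut | V, 2-year cut | √(V₂/V₁) |
|---|---|---|---|---|
| At the median | 14.6 | 1.014 | 1.000 | 0.993 |
| At the median | 19 | 1.086 | 1.000 | 0.960 |
| 24 months | 14.6 | 2.711 | 2.125 | 0.885 |
| 24 months | 19 | 1.759 | 1.400 | 0.892 |

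The later cut reduces the standard error by about 1% to 4% at the median and by about 11% at 24 months.

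**Step 3. Why the median is little affected.** At the 1-year cut, the share with potential follow-up shorter than the median is (14.6 − 12)/24 = 11% or (19 − 12)/24 = 29%. Many of these patients die before they would be censored. The share actually censored before the median is (1/A)∫S(u)du from 12 months to the median, which is about 6% or 17%.

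**Step 4. PFS.** The article gives no PFS median. For assumed medians of 5 to 9 months, the formula of Step 1 gives 37.8 against 39.6 events and 32.8 against 37.1 events of 40. The early cut then leaves out about 2 to 4 events, fewer than for OS.

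**The case against.** The strongest reply is that the passages can be read together: evaluation at 1 year, observation to 2 years. A reader might infer that the article gives two conflicting ends of observation. It does not. The Interim analysis section dates an evaluation and leaves the length of observation open, and the sample-size section's 1 year is what the primary endpoint needs. This part of the reply stands. But under the compatible reading, the second year falls outside the only final survival analysis described. If the 2 years is instead a slip, no collected data are lost, but the abstract is wrong.

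A reader might also infer that the median will be heavily censored. The figures do not support that: only about 6% to 17% of patients are censored before it. A calculation from total deaths, √(26.5/32.4) = 0.90, suggests an interval about 10% narrower with the later cut. It describes an exponential model's rate, not the Kaplan-Meier estimate at the median.

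Nor does the early cut mean that only half the patients inform 2-year survival. Half have potential follow-up of 24 months or more, but every patient contributes until death or censoring. No 2-year survival rate is named as an endpoint.

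Finally, the full protocol or analysis plan, not shown here, may provide a survival update, so it cannot be concluded that the data would be discarded. That is fair. What remains is that the article does not stay silent on the timing: it prints a date for the final evaluation of the secondary endpoints, and that date precedes its own end of observation.

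**Conclusion.** The point holds as a modest and cheaply corrected one. As written, the final OS and PFS evaluation comes a year before the observation stated in the abstract ends, and the 1-year date is justified only for the primary endpoint. If both dates stand, about 6 deaths of 40 patients fall outside the stated final analysis. Precision suffers little at the median (1% to 4%) and more visibly at 24 months (about 11%).

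These sizes rest on exponential survival, uniform accrual, no dropout, and medians taken from earlier studies rather than from an expectation stated for this trial. OS is counted from primary diagnosis, less than 4 weeks before registration. This lengthens the minimum OS follow-up to at most about 13 months, still below both medians.

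OS and PFS are secondary and carry no formal hypothesis. The toxicity decision, the interim rule and the sample size are unaffected.

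**What to change.** First establish which observation period is intended.

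- **If 2 years is intended:** evaluate toxicity and feasibility 1 year after the last inclusion, and make the final OS and PFS analysis at the end of observation, 2 years after the last inclusion. Any survival results reported at 1 year should be labelled as preliminary. Say at which of the two cuts quality of life is finally evaluated.
- **If 1 year is intended:** correct the abstract. The evaluation date can then stay as it is.

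In either case, state the same observation period in the abstract, the sample-size section and the Interim analysis section, and give its length where the formal end of the study is defined.

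The first option costs a second data cut and final survival results one year later. It needs no additional patients and no observation beyond what the abstract already plans. The second option costs only a correction of wording.
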